### Sample size estimation

The primary aim in this study is to detect a 5% difference in LVEF as measured by CMR between the control and intervention group after 12 months. Using a two sample t test and assuming a mean LVEF of 67% in the control arm and equal Standard Deviation in each group of 6% [27], a study of 64 participants (32 per group) would permit the detection of a 5% difference in LVEF from baseline to 12 months between the intervention and control groups, with 90% power at 5%, 2-sided significance level. Allowing for study attrition and death of 10%, we aim to recruit 72 participants to achieve an evaluable sample of 64 participants.

### Statistical methods

All the continuous variables will be tested for normality using their histograms and normality tests. The primary endpoint will be compared between the two groups at specific time points using the Mann U Whitney or Independent T-test. Repeated measures analysis will be used for testing the difference on primary endpoint between tests across the whole period. Poisson regression analysis will be used for comparing the frequency of intra-dialytic RWMAs between the two groups. Haemodynamic variables and other secondary endpoints will be analysed using repeated measures and Bonferroni’s test for multiple comparisons. Paired tests, Wilcoxon Signed test or Paired T-test, will be used for comparing the primary and secondary endpoints between two time points within each group. An alpha error at 0.05 will be judged as significant. Analysis will be performed using SPSS for Windows, v16 or Stata v10. Statistical analysis will be based on an intention-to-treat principle with all data analysed according to the patient’s original study group allocation regardless of death, crossover or early withdrawal.

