### Cardiac and cerebral magnetic resonance imaging

Contrast-free cardiac and cerebral MRI will be performed at baseline and 12 months when the patient has been established on HD with a stable dry weight unchanged for at least 4 weeks. Studies will occur on non-dialysis days at two centres using a 1.5 T MRI scanner (GE Signa HDxt 1.5 T, GE Healthcare, Milwaukee,US). Acquisition will include serial contiguous short-axis cines piloted from vertical or horizontal long axis of the left ventricle using ECG-gated steady-state in free precession sequences in accordance with validated methodologies [27]. Analysis will be performed with the anonymised images off-line by planimetry using commercially available software for assessment of ventricular volumes and mass. Brain MRI will examine the integrity and microstructure of white matter using diffusion tensor imaging. The anonymised images will be analysed off-line for diffusivity and anisotropy corrected for brain volume.

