### Primary study outcome

Change in resting LVEF by cardiac magnetic resonance (CMR) at 12 months compared to baseline between the intervention and control group.

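### Two between-group analyses of LVEF are listed, neither is named as primary and neither adjusts for baseline LVEF; one ANCOVA would be more precise at almost no cost

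*Protocol article*

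**What the plan says.** Under Primary study outcome, the protocol article gives the endpoint as "Change in resting LVEF by cardiac magnetic resonance (CMR) at 12 months compared to baseline between the intervention and control group". Each patient therefore contributes one change value, because "Contrast-free cardiac and cerebral MRI will be performed at baseline and 12 months" and at no other time.

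Under Statistical methods, three analyses of that endpoint are listed:

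- A two-group test: "The primary endpoint will be compared between the two groups at specific time points using the Mann U Whitney or Independent T-test".
- A longitudinal analysis: "Repeated measures analysis will be used for testing the difference on primary endpoint between tests across the whole period".
- Paired tests, which "will be used for comparing the primary and secondary endpoints between two time points within each group".

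None is called primary, no covariate is mentioned, and the term to be tested in the repeated measures analysis is not identified.

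Under Sample size estimation, the calculation is framed in levels: "Using a two sample t test and assuming a mean LVEF of 67% in the control arm", with an SD of 6% in each group. The same sentence describes the target as change: the sample "would permit the detection of a 5% difference in LVEF from baseline to 12 months" between the groups, "with 90% power at 5%, 2-sided significance level".

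**The concern.** The endpoint is a single change per patient, but the first listed test is made at more than one time. A change score exists only once, so the sentence fits LVEF levels better. The paired within-arm tests of the same endpoint point the same way, since they make sense only for levels. Read so, the 12-month comparison makes no use of the baseline scan, although one is planned for every patient.

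The repeated measures analysis does use the baseline scan, but its natural between-group term is a change-score test. That test over-corrects for baseline when the two scans are only moderately correlated. The paired tests do not compare the arms at all.

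Two things are at stake. First, the trial could report two between-group results for its primary endpoint with no stated order between them. Second, with about 32 evaluable patients per arm, both approaches leave precision unused that the planned scans could supply.

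**Working it through.** **Inputs from the article.** Difference 5 LVEF points; SD 6; 32 evaluable per arm; two-sided alpha 0.05; 90% power; 10% attrition (Sample size estimation). CMR at baseline and 12 months (imaging section).

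**Input not in the article.** The correlation ρ between baseline and 12-month LVEF. I assume 0.3, 0.5 and 0.7, with the same SD at both times and in both arms.

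**Step 1: reproduce the stated sample size.** For a two-sample t-test on levels, SE = 6 × √(2/32) = 1.5 and the noncentrality is 5/1.5 = 3.33 on 62 degrees of freedom. Power is 90.7%, and 32 is the smallest number per arm that reaches 90%. Then 64/0.9 = 71.1, rounded up to 72. The article's figures reproduce.

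**Step 2: SD of each candidate analysis.**

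- Levels at 12 months: SD = 6, whatever ρ is.
- Change (the group-by-time term with two time points): SD = 6√(2(1−ρ)). In a simulated data set with 32 per arm, the group-by-time t statistic and the t-test on change were both 5.731.
- ANCOVA: residual SD = 6√(1−ρ²).

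**Step 3: power at 32 per arm (number per arm needed for 90% in brackets).**

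| ρ (assumed) | Levels | Change: SD, power | ANCOVA: SD, power |
|---|---|---|---|
| 0.3 | 90.7% (32) | 7.10, 79.2% (44) | 5.72, 93.1% (29) |
| 0.5 | 90.7% (32) | 6.00, 90.7% (32) | 5.20, 96.6% (24) |
| 0.7 | 90.7% (32) | 4.65, 98.9% (20) | 4.28, 99.6% (17) |

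All rows use 62 degrees of freedom. ANCOVA has 61, and the critical value is about 2.00 either way.

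**Step 4: why the ordering does not depend on the assumed ρ.** Relative to the variance of levels, the multipliers are 1 for levels, 2(1−ρ) for change and 1−ρ² for ANCOVA. The first exceeds the third by ρ², and the second exceeds the third by (1−ρ)². For any ρ strictly between 0 and 1, ANCOVA therefore has the smallest variance. Its reduction against levels is 9%, 25% and 49% at ρ = 0.3, 0.5 and 0.7. Levels and change swap places at ρ = 0.5, so which of the two listed analyses is better depends on a quantity the article does not give.

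**Step 5: effect of a chance baseline gap.** With SD 6 and 32 per arm, the SE of the baseline difference is also 1.5 points, so a gap larger than that occurs in about one trial in three. Given a 1.5-point gap, the level difference is shifted by 1.5ρ (0.45, 0.75 and 1.05 points). The change difference is shifted the other way by 1.5(1−ρ) (1.05, 0.75 and 0.45 points). ANCOVA removes both shifts.

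**Step 6: the repeated measures term.** If the term tested were the group effect averaged over both times, the expected difference would be 2.5 and the SD 6√((1+ρ)/2). Power would then be 53.0%, 47.4% and 42.8%. The article does not say that this term is intended; the figures show why it should be named.

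**The case against.** The strongest reply is that nothing here is invalid, and most of it stands.

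- A reader might infer that the baseline scan is discarded. The text does not support that: the sentence after the t-test plans a repeated measures analysis, which must use both scans, and the paired tests use both as well.
- A reader might infer that the t-test targets the wrong quantity. Under 1:1 randomisation the expected baseline means are equal, so the difference in 12-month levels and the difference in change have the same expectation. A chance baseline gap is already covered by the test's standard error and does not inflate type I error. The loss is precision, not bias.
- A reader might infer a power shortfall. On the article's own inputs there is none: 90.7% against a stated 90%.
- A reader might infer a planned significance test between arms at baseline. The wording allows this but does not state it.
- The t-test sentence speaks of the primary endpoint, which the article defines as change. It could therefore mean a t-test on change, which uses the baseline. Testing at several times fits that reading poorly, but the text is ambiguous rather than plainly a test of levels.

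It can also be said that covariates are commonly left to a fuller document, which is not shown. That is fair, and it lowers the weight of the point. It does not remove it, because this section does state its tests. As stated, they leave two between-group analyses of one endpoint without an order, and on either reading neither conditions on baseline.

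**Conclusion.** The point holds as an improvement in efficiency and clarity, not as an error. The listed between-group analyses are valid, and the level test delivers the stated power. Neither is named as primary, and both are less precise than a baseline-adjusted comparison.

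At 32 per arm, the gain over levels is 2.4, 5.9 and 8.9 percentage points of power at ρ = 0.3, 0.5 and 0.7 (93.1, 96.6 and 99.6, each less 90.7). Over change it is 13.9, 5.9 and 0.7 points (93.1 − 79.2, 96.6 − 90.7, 99.6 − 98.9). The gain is therefore small against levels at low correlation and small against change at high correlation. ANCOVA is the one choice that does well across the range.

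These sizes rest on the article's SD of 6 and on the assumed correlations. The direction needs only a correlation strictly between 0 and 1, ignoring the one degree of freedom.

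**What to change.** In Statistical methods, name one primary analysis. Suggested wording: the primary analysis is a linear model of 12-month CMR LVEF on allocated group with baseline CMR LVEF as covariate; the adjusted mean difference and its 95% confidence interval will be reported.

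Describe the t-test or Mann-Whitney comparison, the repeated measures analysis and the within-group paired tests as supportive. If the repeated measures analysis is kept, name group-by-time as the term of interest. State that baseline LVEF will be described by arm and not tested between arms.

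The cost is a few sentences and one degree of freedom. No new data are needed, since the baseline scan is already planned, and the sample size need not change.

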**Methods/Design:**

The trial is a multicentre, prospective, randomised, un-blinded, controlled trial. Patients will be randomised 1:1 to use a dialysate temperature of 37°C for 12 months or an individualised cooled dialysate. The latter will be set at 0.5°C less than the patient’s own temperature, determined from the mean of 6 prior treatment sessions with a tympanic thermometer, up to a maximum of 36°C. Protocol adherence will be regularly checked. Inclusion criteria are incident adult HD patients within 180 days of commencing in-centre treatment 3 times per week with capacity to consent for the trial and without contra-indications for magnetic resonance imaging. Exclusion criteria include not meeting inclusion criteria, inability to tolerate magnetic resonance imaging and New York Heart Association Grade IV heart failure. During the study period, resting cardiac and cerebral magnetic resonance imaging will be performed at baseline and 12 months on an inter-dialytic day. Cardiovascular performance during HD will also be assessed by continuous cardiac output monitors, intra-dialytic echocardiography and biomarkers at baseline and 12 months. The primary outcome measure is a 5% between-group difference in left ventricular ejection fraction measured by cardiac magnetic resonance imaging at 12 months compared to baseline. Analysis will be by intention-to-treat. Secondary outcome measures will include changes in cerebral microstructure and changes in cardiovascular performance during HD. A total of 73 patients have been recruited into the trial from four UK centres. The trial is funded by a Research for Patient Benefit Grant from the National Institute of Healthcare Research. AO is funded by a British Heart Foundation Clinical Research Training Fellowship Grant. The funders had no role in the design of the study.

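### Several analyses of primary LVEF are listed at 0.05 without saying which one decides the trial, and the abstract writes a 5% threshold into the outcome that the primary outcome section does not have

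*Protocol article*

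**What the plan says.** The Primary study outcome section defines a single outcome: the change in resting LVEF by CMR from baseline to 12 months, compared between groups. It gives no threshold. The Sample size estimation section plans for one test ("Using a two sample t test"), "with 90% power at 5%, 2-sided significance level".

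The Statistical methods section is less settled. It opens with "All the continuous variables will be tested for normality using their histograms and normality tests" and then applies to the primary endpoint:

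- a Mann-Whitney or independent t-test between groups at specific time points;
- repeated measures: "Repeated measures analysis will be used for testing the difference on primary endpoint between tests across the whole period";
- a paired t-test or Wilcoxon test between two time points within each group, stated to cover both primary and secondary endpoints.

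One rule follows for everything: "An alpha error at 0.05 will be judged as significant". Bonferroni appears only in the sentence on haemodynamic and other secondary endpoints.

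The abstract words the outcome differently: "The primary outcome measure is a 5% between-group difference in left ventricular ejection fraction".

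**The concern.** The listed analyses answer different questions, and the text does not say which one settles the primary hypothesis.

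- A comparison at specific time points reads most naturally as a comparison of LVEF levels. CMR is done only at baseline and 12 months, so that means a baseline comparison and a 12-month comparison. Neither is the change that the outcome section defines.
- A Mann-Whitney test does not estimate a mean difference in LVEF, which is the quantity the sample size is built on. Choosing it after seeing the distribution leaves the estimand open until the data are in.
- A paired test within an arm is not a comparison of treatments at all. A fall in LVEF shared by both arms can make it significant in one arm only.

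If the results disagree, the article gives no basis for deciding whether the trial succeeded. The 5% threshold in the abstract adds a second uncertainty, about what an observed difference smaller than 5 points would mean.

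**Working it through.** **Inputs from the Sample size estimation section.** Difference 5 points ("The primary aim in this study is to detect a 5% difference in LVEF as measured by CMR"); SD 6 in each group ("assuming a mean LVEF of 67% in the control arm and equal Standard Deviation in each group of 6"%); 32 per group; two-sided 5%; 90% power; 10% attrition. **Assumption, not in the documents:** the correlation r between baseline and 12-month LVEF, taken as 0.3 to 0.7.

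**1. The plan's own figure.** The standard error of a difference between two means is 6 × √(2/32) = 1.5. With a noncentrality of 5/1.5 = 3.33 on 62 degrees of freedom, the exact t-test has 90.7% power, and 32 is the smallest group size that reaches 90%. Then 64/0.9 = 71.1, rounded up to 72. The sample size reproduces.

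**2. False-positive rate by reading.** Simulation with no treatment effect: 32 per arm, SD 6, LVEF stable in both arms, 100,000 trials per correlation, each test at two-sided 0.05.

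| What may count as success | Rate, r = 0.3 to 0.7 |
|---|---|
| Between-group test of change only | 5% |
| 12-month test or change test | 9.0% to 9.4% |
| The same, plus a group effect averaged over both scans | 11.1% to 11.6% |
| 12-month or change test, plus the two within-group tests | 15.1% to 15.6% |

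With two scans, the group-by-time test in a repeated-measures model is the same test as the t-test on change. That is why the first row can hold even with repeated measures listed. For comparison, two independent tests would give 1 − 0.95² = 9.75%.

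Taking the better of the t-test and Mann-Whitney on the same normal data gives 5.9% (20,000 trials), so that choice alone adds little to the error rate.

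The within-group tests depend heavily on the assumption of stable LVEF. With a shared fall of 2 points and r = 0.5, at least one is significant in 69% of null trials, and exactly one arm is significant in 49%.

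**3. The 5% threshold.** The smallest significant observed difference in the 12-month t-test is t(0.975; 62) × 1.5 = 1.999 × 1.5 = 3.0 points. A result between 3.0 and 5 points would be significant under the Statistical methods section but would fall short of the outcome as the abstract words it. If an observed change difference of at least 5 points were required as well as significance, the false-positive rate would fall to 1.9% or less (r from 0 to 0.9). The threshold cannot raise it.

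**4. Power of the candidate primary tests for a true 5-point difference.** The SD is 6 for the 12-month level, 6√(2(1 − r)) for change, and 6√(1 − r²) after adjustment for baseline (61 degrees of freedom).

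| r | 12-month t-test | Change t-test | Baseline-adjusted |
|---|---|---|---|
| 0.3 | 90.7% | SD 7.10: 79.2% | SD 5.72: 93.0% |
| 0.5 | 90.7% | SD 6.00: 90.7% | SD 5.20: 96.6% |
| 0.7 | 90.7% | SD 4.65: 98.9% | SD 4.28: 99.6% |

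The adjusted comparison has the highest power in every row.

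**The case against.** The strongest reply is that the endpoint and the design test are both single. On the outcome section's definition, the t-test on change and the group-by-time test coincide, and the error rate is 5%. The article condenses a longer protocol, and ranking primary against supportive analyses is often left to an analysis plan. This stands as far as it goes: nothing says that a win on any one test is enough. It does not remove the ambiguity, because the article does list the tests of the primary endpoint, and its reference to specific time points does not fit the change endpoint.

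A reader might infer three stronger things that the documents do not support:

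- That the trial's false-positive rate is about double the stated level. That figure needs an any-win rule, which the text does not contain.
- That the 5% threshold contributes to inflation. As an added requirement it lowers the error rate, and as a planning difference it has no effect. Any trial with 90% power can reach significance below its design difference.
- That the repeated-measures analysis has only about 43% to 53% power. This holds for a group effect averaged over baseline and 12 months, which halves the effect to 2.5 points. The text does not specify that contrast, and group-by-time is the usual one for two scans.

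The text also offers the t-test or the Mann-Whitney test, not the better of the two.

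**Conclusion.** The concern holds as a lack of definition, not as a demonstrated error rate. The article does not say which analysis of primary LVEF decides the trial. The false-positive rate therefore depends on the reading: 5% if only the between-group test of change decides, about 9% if either the 12-month or the change comparison may count, and about 15% if within-group tests may count as well. The last two figures rest on 32 per arm, an assumed correlation of 0.3 to 0.7 and LVEF stable in both arms. With a shared decline, the within-group figure would be much higher.

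The abstract's threshold is a separate inconsistency with the outcome section. Its consequence is an unclear interpretation of observed differences between 3 and 5 points, not inflation. The sample size is correct on its stated inputs.

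**What to change.** 1. Name one primary analysis: the between-group difference in 12-month LVEF adjusted for baseline LVEF, two-sided 0.05, with a 95% CI, used irrespective of the normality tests. It uses a baseline scan that the trial already collects.
2. Label the Mann-Whitney, repeated-measures and within-group paired analyses of LVEF as supportive, and state that no claim of benefit will rest on a within-group test.
3. Reword the abstract to match the Primary study outcome section, with 5 points given as the planning difference against which the CI is interpreted.

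The cost is wording only: no extra patients, scans or visits. The analysts give up the choice of test after seeing the data. The Trial completion section places analysis after follow-up ends in January 2013, so on that timetable the change can be made before the primary analysis.

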### Haemodialysis induced myocardial ischaemia

In the setting of coronary artery disease without kidney disease, transient myocardial ischaemia may lead to left ventricular dysfunction that can persist for several hours after the return of normal perfusion, but is eventually followed by functional recovery. This reversible post-ischaemic dysfunction is known as myocardial stunning. Repetitive episodes of stunning are cumulative eventually leading to hibernation then irreversible contractile dysfunction [1]. The ability of HD to induce myocardial ischaemia had been long suspected with reports of silent, reversible ischaemic ECG changes during HD older than twenty years. Other studies showed elevated cardiac troponins were common and up to 30% of HD treatments were complicated by significant intra-dialytic hypotension [2]. These data suggested HD might induce myocardial ischaemia but were unable to prove this or elucidate the pathophysiology. Subsequent proof-of-concept studies by our group and others in subjects with normal coronary arteries have demonstrated that HD is characterised by a 30% reduction in regional myocardial blood flow by H_2_^15^O positron emission tomography [3]. The decreased myocardial blood flow localises to the same segments as regional wall motion abnormalities (RWMAs) using simultaneous 2D-echocardiography at peak-stress, 15 minutes before the end of a HD treatment compared to pre-HD [3]. This supported use of these stress-RWMAs as a practical surrogate for myocardial ischaemia. These changes in the absence of coronary artery disease can be explained by decreased coronary flow reserve which is well described in dialysis populations [4] and is in turn promoted by a high prevalence of autonomic dysfunction, endothelial dysfunction, left ventricular hypertrophy and arterial stiffness. These factors may underlie the reduced sensitivity and specificity of ischaemia stress testing in HD patients [5]. The HD procedure involves a rise in core temperature, extracorporeal circuit, fluid removal and exposure to a dialysis membrane which combine to form a haemodynamic stress provoking demand ischaemia [6]. Our natural history study of 70 prevalent HD patients showed that compared to pre-HD echocardiography, new RWMAs developed at peak-stress in 45 participants and this associated with 30% mortality and 13% reduction in mean left ventricular ejection fraction by 1 year [7,8]. RWMAs persisted at follow-up in the 36/45 survivors of the subgroup. In the cohort who had no abnormal segments at the start of the study, new segmental RWMAs had also developed. Multivariable analysis showed the significant determinants of these stress-RWMAs were age, ultrafiltration volume, intra-dialytic hypotension and serum troponin-T concentration and this displaced all other variables including diabetes status and history of ischaemic heart disease [7]. In short, the RWMAs characterise those who suffer ischaemia due to the haemodynamic stress of HD. Regardless of the balance of micro- and macrovascular disease in the pathophysiology, reducing these RWMAs represents a valid target and may lead to detectable amelioration of global ventricular function.

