### Assessing cardiovascular performance during HD

Detailed characterisation of cardiovascular performance will be assessed during HD at baseline and 12 months. This occurs during the patient’s usual HD session in their own centre using the same portable data collecting instruments across all centres. 2-dimensional echocardiography will be performed using commercially available equipment (1.5-4Mhz probe, Vivid-I, GE Healthcare) by one of two trained technicians in the left lateral position. Sector width, frequency and depth will be adjusted to produce optimal border definition and a frame-rate of 50–80 per second. Standard apical 2 and 4-chamber image loops will be recorded pre-dialysis (rest) and 15 minutes before the end of dialysis (stress). Image loops will be anonymised and analysed off-line in random order for regional deformation using dedicated software (EchoPac, GE Vingmed). Continuous non-invasive cardiac output monitoring will be recorded using a thoracic bioreactance monitor (NICOM™, Cheetah Medical). This uses phase changes in alternating electrical current to derive cardiac output. This endows a greater precision and signal-to-noise ratio than impedance cardiography. The monitor is validated in both healthy and co-morbid adults [29]. The Finometer™ (TNO Instruments) utilises a finger-cuff to detect beat-to-beat changes in digital arterial pressure and calibrates this against oscillometric brachial artery pressure. The Finometer™ is validated in critical care and HD settings [30].

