### Secondary study outcomes

 · Left ventricular mass by CMR

 · Regional myocardial deformation by speckle-tracking echocardiography and CMR tagging.

 · A range of haemodynamic variables, including cardiac output, pulse rate, heart rate and frequency of intra-dialytic hypotension

 · Change in body composition by bioimpedance

 · Change in cerebral diffusion tensor MRI

 · Change in cognitive assessment scores

 · Change in soluble cardiac biomarkers

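### Poisson regression for intra-dialytic RWMA frequency: its variance assumption is unlikely to hold for a bounded count of segments from one heart, and the plan names no variance that would protect the test

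*Protocol article*

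**What the plan says.** Under Statistical methods the article fixes the model: "Poisson regression analysis will be used for comparing the frequency of intra-dialytic RWMAs between the two groups". That section mentions no dispersion term, robust variance or denominator.

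The nature of the outcome has to be pieced together from other sections:

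- Haemodialysis induced myocardial ischaemia treats RWMAs as properties of segments of the ventricle: "In the cohort who had no abnormal segments at the start of the study, new segmental RWMAs had also developed". It also reports a patient-level figure from a cohort of 70 prevalent patients: "new RWMAs developed at peak-stress in 45 participants".
- Rationale for cooling describes the pilot results as a proportion of patients developing RWMAs, which is a second possible meaning of frequency.
- Assessing cardiovascular performance during HD says that loops come from the apical 2- and 4-chamber views only, before dialysis and near its end. On timing it says: "Detailed characterisation of cardiovascular performance will be assessed during HD at baseline and 12 months".

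The article does not say whether frequency means abnormal segments per patient or patients with any abnormality. It also does not give the number of segments read.

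**The concern.** A Poisson model suits events that can recur without a practical ceiling and whose variance equals their mean. A count of abnormal segments departs from this in two ways. It cannot exceed the number of segments read, which pulls the variance below the mean. The segments also share one heart, one ultrafiltration load and one blood pressure course, so they probably become abnormal together, which pushes the variance above the mean. Model-based standard errors are right only if the two effects happen to cancel.

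Reduction of RWMAs is the mechanism on which the rationale for cooling rests, and the Discussion expects the explanatory outcomes to give insight into mechanism and to help justify a larger study. Standard errors that are too small would produce false mechanistic claims; standard errors that are too large would hide a real effect.

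**Working it through.** **Inputs from the article.** Arm size is 32 evaluable patients (Sample size estimation). That figure reproduces: for a 5-point difference and SD 6, the exact two-sample t-test has 89.8% power with 31 per arm and 90.7% with 32, and 64/0.9 = 71.1, rounded up to 72. It is used here only as the arm size. The patient-level RWMA frequency in the previous cohort is 45/70 = 64%.

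**Inputs assumed.** The article gives none of these: segments read m = 12; proportion abnormal p from 0.086 to 0.25; within-heart correlation ρ from 0 to 0.3. One count per patient at a single time point, no treatment effect.

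**Formula.** For m segments with common correlation ρ,

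φ = variance/mean = (1 − p)(1 + (m − 1)ρ).

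The Poisson standard error is wrong by a factor √φ. The approximate true error of a nominal 5% two-sided test is 2[1 − Φ(1.96/√φ)].

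Example: p = 0.25, ρ = 0.2 gives φ = 0.75 × (1 + 11 × 0.2) = 0.75 × 3.2 = 2.40, √φ = 1.55, and an error of 2[1 − Φ(1.265)] = 0.206.

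**Results** (φ by formula; errors by beta-binomial simulation, 40,000 null trials per cell):

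| p | ρ | φ | Poisson, model-based | Poisson, robust variance |
|---|---|---|---|---|
| 0.086 | 0 | 0.91 | 3.9% | 5.2% |
| 0.086 | 0.03 | 1.22 | 7.0% | 5.1% |
| 0.086 | 0.1 | 1.92 | 15.2% | 5.7% |
| 0.086 | 0.3 | 3.93 | 32.2% | 6.7% |
| 0.25 | 0 | 0.75 | 2.3% | 5.3% |
| 0.25 | 0.03 | 1.00 | 4.9% | 5.2% |
| 0.25 | 0.1 | 1.58 | 11.4% | 5.2% |
| 0.25 | 0.3 | 3.22 | 27.8% | 5.0% |

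**Where the two effects cancel.** φ = 1 when ρ = p/[(1 − p)(m − 1)]. At m = 12 this is 0.086/(0.914 × 11) = 0.009 for p = 0.086 and 0.25/(0.75 × 11) = 0.030 for p = 0.25. Over m from 10 to 16 and p from 0.1 to 0.4 it runs from 0.007 to 0.074. Below that value the test is conservative; above it, anticonservative.

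**If frequency means patients with any RWMA.** The outcome is then binary, and φ = 1 − 45/70 = 0.36. The model-based Poisson test has an error of 2[1 − Φ(1.96/√0.357)] = 0.1%, against about 4% by simulation with robust variance. For an assumed 64% versus 32% with 32 per arm, simulated power is 42% model-based and 69% robust.

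**Does 45 of 70 settle the direction?** No. The share with no new RWMA is 25/70 = 36%. A Poisson count gives this at mean −ln(0.357) = 1.03, or 1.03/12 = 8.6% of 12 segments, which is the source of the lower value of p. Independent segments give it at p = 1 − 0.357^(1/12) = 8.2%, where φ is below 1. A beta-binomial with 20% of segments abnormal gives it at ρ of about 0.28, where φ = 0.8 × (1 + 11 × 0.28) = 3.3. One zero fraction fits under-, equal and overdispersion alike.

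**The case against.** The strongest reply is that the article names a model family and leaves the variance estimator to a plan not shown. Poisson regression with robust variance is still Poisson regression, and in the check above it holds its level at about 4-7%. This limits the point: the mean model is not the mistake, and silence on detail would not be a finding by itself. But the article does commit to a model, and on its ordinary reading that model uses a variance which does not suit the outcome described.

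A second reply is that every figure rests on assumed segment numbers, prevalence and correlation. That stands. The figures show sensitivity; they do not estimate what will happen in this trial.

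A reader might infer more, in four ways that the article does not support:

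- *That the standard errors are certain to be too small.* The ceiling and the correlation act in opposite directions, so the sign is not determined.
- *That 45 of 70 proves segments fail together.* As shown, the same figure fits a Poisson count. It also comes from prevalent patients, whereas this trial enrols incident ones.
- *That the model ignores the baseline assessment.* The wording is compatible with a baseline term.
- *That hypotension, a true event count, has been wrongly sent to a normal-theory method.* Secondary study outcomes lists haemodynamic variables as "including cardiac output, pulse rate, heart rate and frequency of intra-dialytic hypotension", and Statistical methods says: "Haemodynamic variables and other secondary endpoints will be analysed using repeated measures". That wording names no distribution and does not exclude a count model, and no session window is given. It is not shown to be an error and is not raised as one.

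**Conclusion.** The point holds in a limited form. Plain Poisson regression is poorly matched to RWMA frequency on either reading of the term. For a segment count, with 12 segments, 32 per arm and 8.6% to 25% of segments abnormal, the true error at nominal 5% is about 2-4% with no correlation, 5-7% at 0.03 and 12-32% at 0.1 to 0.3. It is close to nominal only in a narrow band of low correlation. For patients with any RWMA at 64%, it is about 0.1%, with an appreciable loss of power.

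The direction and size of the error in this trial cannot be known from the article. The change is worth making because the same remedy covers every case. The outcome is mechanistic and is not named as such among the secondary outcomes, where regional myocardial deformation is the nearest entry. The primary LVEF comparison and its sample size are unaffected.

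**What to change.** Amend the sentence on RWMAs under Statistical methods, before outcome data are examined, to do the following:

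1. Define the variable: abnormal segments out of segments read per patient, or patients with any RWMA.
2. For segments, use a binomial-type model with the number read as denominator, or keep the Poisson mean model. In both cases use robust or scaled variance at the patient level. A negative binomial model would allow overdispersion but has no ceiling, so it is not the first choice here.
3. For patients with any RWMA, use a binary-outcome model, or Poisson regression with robust variance.
4. Adjust for the baseline RWMA count and report the effect with a 95% confidence interval.

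The cost is a few sentences and standard commands, with no new data beyond recording how many segments were read. Confidence intervals for a segment count will probably be wider than plain Poisson intervals.
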